## Abstract

**Purpose:**

Severe acute respiratory syndrome coronavirus 2 (SARS-CoV-2) has spread worldwide causing a global health emergency. Pa-COVID-19 aims to provide comprehensive data on clinical course, pathophysiology, immunology and outcome of COVID-19, to identify prognostic biomarkers, clinical scores, and therapeutic targets for improved clinical management and preventive interventions.

**Methods:**

Pa-COVID-19 is a prospective observational cohort study of patients with confirmed SARS-CoV-2 infection treated at Charité - Universitätsmedizin Berlin. We collect data on epidemiology, demography, medical history, symptoms, clinical course, and pathogen testing and treatment. Systematic, serial blood sampling will allow deep molecular and immunological phenotyping, transcriptomic profiling, and comprehensive biobanking. Longitudinal data and sample collection during hospitalization will be supplemented by long-term follow-up.

**Results:**

Outcome measures include the WHO clinical ordinal scale on day 15 and clinical, functional, and health-related quality-of-life assessments at discharge and during follow-up. We developed a scalable dataset to (i) suit national standards of care, (ii) facilitate comprehensive data collection in medical care facilities with varying resources, and (iii) allow for rapid implementation of interventional trials based on the standardized study design and data collection. We propose this scalable protocol as blueprint for harmonized data collection and deep phenotyping in COVID-19 in Germany.

**Conclusion:**

We established a basic platform for harmonized, scalable data collection, pathophysiological analysis, and deep phenotyping of COVID-19, which enables rapid generation of evidence for improved medical care and identification of candidate therapeutic and preventive strategies. The electronic database accredited for interventional trials allows fast trial implementation for candidate therapeutic agents.

**Trial registration:**

Registered at the German registry for clinical studies (DRKS00021688)

**Electronic supplementary material:**

The online version of this article (10.1007/s15010-020-01464-x) contains supplementary material, which is available to authorized users.

## Introduction

Lower respiratory tract infections cause several millions of deaths every year and remain the most deadly communicable disease as reported by WHO (Global Health Observatory (GHO) data of the WHO, 2018). Comprehensive phenotyping of diseases caused by new infectious agents is required to enhance the understanding of their pathophysiology, to improve clinical management, and to develop therapeutic agents. In the past 20 years alone, zoonotic viruses have caused multiple outbreaks, which all involved respiratory infections. In November 2003, Severe Acute Respiratory Syndrome (SARS) virus caused a global disease outbreak with > 8000 infections and 774 deaths [1]. In 2012, the first infection with a new Coronavirus, the Middle-East Respiratory Syndrome Coronavirus (MERS-CoV), was recorded [2]. Despite global spread by travelers [3, 4], MERS-CoV remains largely confined to the Arabian Peninsula. In December 2019, first cases of what was later identified as infections with a novel coronavirus, termed SARS-CoV-2, emerged in Wuhan, China [5]. The local outbreak has rapidly evolved into a global health emergency (WHO Director-General's statement, 30th January 2020). SARS-CoV-2 is highly contagious by human-to-human transmission [6, 7] and can be transmitted by pre- or oligo-symptomatic individuals [8]. According to WHO, by the middle of April, there are more than 2,000,000 confirmed infections with > 120,000 deaths worldwide.

Rapid generation of meaningful evidence for improved clinical management of COVID-19 requires harmonized phenotyping and comparable data collection in a well-defined patient population. Besides decade-long experience in multicentric phenotyping and clinical studies of community acquired pneumonia (CAPNETZ, PROGRESS, and CAPSyS) [9, 10], Berlin has strong expertise in the areas of coronavirus biology and diagnostics [11–17], infectious diseases and highly contagious diseases, immunology of infections and vaccines, respiratory medicine and intensive care, and clinical management of ARDS [18, 19].

This unique local expertise together with the global burden of COVID-19 implies a special responsibility in assessing all available information drawn from medical care and human biomaterial within Charité as well as gathering patient data nationwide to enable fighting the outbreak of SARS-CoV-2 infection in a systematic and effective way.

*The aim of Pa-COVID-19: *harmonized deep clinical, molecular, and immunological phenotyping in patients with COVID-19 to (i) elucidate the pathophysiology of the disease, (ii) identify diagnostic and prognostic scores and biomarkers for improved clinical management, (iii) identify putative therapeutic targets, (iv) produce evidence regarding short- and long-term clinical outcomes, and (v) identify correlates of protective immunity. Longitudinal data- and bio-sampling as well as post-mortem analysis will enable for characterization of clinical features of distinct disease courses and identify determinants of severity and transmission.

## Methods

### Study design

Pa-COVID-19 is a prospective observational cohort study. All patients diagnosed with COVID-19 at Charite - Universitätsmedizin Berlin are eligible for inclusion. The protocol was developed in accordance with and extends upon the standardized protocol for the rapid, coordinated clinical investigation of severe acute infections by pathogens of public health interest published by the International Severe Acute Respiratory and Emerging Infection Consortium (ISARIC) [20].

We aimed to establish a study protocol that can serve as blueprint and central platform for harmonized deep clinical, molecular, and immunological phenotyping studies in COVID-19 patients in Germany. The protocol supports data sharing efforts through adherence to international data harmonization standards. Data are collected longitudinally from patients with confirmed COVID-19 three times per week during their hospitalization and at follow-up visits. Data include epidemiological and demographic parameters, medical history and potential risk factors, documentation of standard of care procedures, and clinical course, including different patterns of organ involvement, quality of care, morbidity, and quality of life. Moreover, extensive serial high-quality bio-sampling consisting of various sample types with deep molecular, immunological, and virological phenotyping through single-cell- and bulk- multi-omics analysis is performed.

Here, we provide a comprehensive protocol for the interdisciplinary characterization of the syndrome caused by infection with SARS-CoV-2, a newly-emerged zoonotic virus and poorly characterized human pathogen. Therefore, the sample size is not prospectively determined. Recruitment of participants will depend on the emergence and spread of the disease in Berlin, Germany, and on the number of patients presenting at Charite - Universitätsmedizin Berlin. With the evolving outbreak, recruitment in other study centers will be considered to facilitate the establishment of a comprehensive clinical and molecular database. The study has no set end date.

### Inclusion criteria

Proven infection with SARS-CoV-2 (positive pathogen testing). Willingness to participate in the study.

### Exclusion criteria

Refusal to participate by patient, parent, or appropriate legal representative.

Any conditions that prohibit supplemental blood sampling.

### Data collection

#### Harmonized scalable dataset/electronic Case Report Form (eCRF)

This protocol outlines the methodology of the Berlin prospective cohort for capturing data of COVID-19. The parameters were selected and adapted to local standards through a multidisciplinary expert review board consisting of clinical researchers at Charité, Department of Infectious Diseases and Respiratory Medicine, Institute of Virology, Departments of Anaesthesiology and Operative Intensive Care Medicine, Department of Psychosomatic Medicine, Department of Pediatrics, Departments of Cardiology, Department of Neurology and Center for Stroke Research, Department of Nephrology and Medical Intensive Care, Department of Endocrinology and Metabolism, Department of Medicine, Division of Gastroenterology, Infectious Diseases and Rheumatology, Department of Hepatology and Gastroenterology, Institute of Tropical Medicine and International Health, Central Biobank Charité (ZeBanC), and the Clinical Study Centre at the Berlin Institute of Health, based on available preliminary data and in accordance with the WHO supported case report form (CRF) proposed by the International Severe Acute Respiratory and Emerging Infection Consortium (ISARIC). Items of the ISARIC–CRF were translated to German using the standardized Functional Assessment of Chronic Illness Therapy (FACIT) translation methodology [21]. Data elements were prioritized into three categories (core data, recommended data, and supplemental data elements, see eCRF, supplementary file 1) to allow the adjustment of data collection to different healthcare and research resources. The latest version of the eCRF is available up-to-date at the study website https://studycenter.charite.de/covid_19/.

In addition to medical history and history of present illness, we aim for detailed longitudinal documentation of (i) clinical symptoms, (ii) vital signs and blood gases, (iii) laboratory parameters (including inflammation markers, cardiac enzymes, coagulation parameters, etc.), (iv) imaging data (e.g., X-ray, echocardiography, ultrasound, CT scans, and MRI scans), (v) microbiological and virological tests, (vi) supplementary diagnostic data (e.g., bronchoscopy and lumbar puncture), (vi) concomitant medication, and (vii) details of clinical interventions (mechanical ventilation, organ replacement therapy, etc.) (Table 1). Patients can also be included in Pa-COVID-19 if they participate in other clinical studies, e.g., in interventional clinical trials. In these patients, trial participation and application of any study medication will be documented in the eCRF. During in-patient stay, the patient-reported health status will be measured using tailored short forms from the Patient-Reported Outcome Measurement Information System^®^ (PROMIS), targeting for precise assessments of dyspnoea and physical function [22]. Overall outcomes will be evaluated using clinician as well as patient-reported health data, including the WHO 7 category ordinal scale [23] at study visits until day 15 and at discharge from hospital. Quality of life, health status, and performance in activities of daily living will be assessed using the Barthel Index and an adapted version of the PROMIS^®^-29 Profile at discharge, 6 weeks, 3 months, 6 months, and 12 months after inclusion. In addition, lung function, blood gases, cardiac function, renal function, occurrence of Post-Intensive Care Syndrome, neuropsychiatric function, exercise capacity, and cognitive function will be assessed in selected patient groups at follow-up visits [24].

**Table 1 Tab1:** Study procedures: each visit during the patient's hospital stay will register as a new visit

Visit	Enrolment											
	V1	V2	V3	V4	V5	V6	V7	V-discharge	V8^a^	V9^a^	V10^a^	V11^a^
Visits will be conducted three times a week until discharge from hospital^e^	Monday/Wednesday/Friday starting day of enrolment							Day of discharge	6 weeks after enrolment	3 months after enrolment	6 months after enrolment	12 months after enrolment
Visit windows	–	–	–	–	–	–		–	± 1 week	± 2 week	± 3 weeks	± 3 weeks
Informed consent/authorization	×											
Epidemiological data	×^d^											
Demographics	×^d^											
Medical history	×^d^								×^d^	×^d^	×^d^	×^d^
Vital signs	×	×	×	×	×	×	×	×				×
Clinical symptoms	×^d^	×^d^	×^d^	×^d^	×^d^	×^d^	×^d^	×^d^	×^d^	×^d^	×^d^	×^d^
Documentation of clinical blood sample results (chemistry, haematology)^b^/routine blood testing	×	×	×	×	×	×	×	×	×	×	×	×
Recording of SARS-CoV-2 PCR testing^b^	×					×	×	×				
SARS-CoV-2 antibody testing^c^	×	×	×	×	×	×	×	×			×	×
Serum cytokines and chemokines, quantitative proteomics, circulating myeloid and lymphoid cells^c^	×	×	×	×	×	×	×	×	×	×	×	×
Banked bio-materials^c^	×	×	×	×	×	×	×	×	×	×	×	×
Concomitant medications	×	×	×	×	×	×	×	×	×^d^	×^d^	×^d^	×^d^
Documentation of clinical records from patient charts, e.g., parameters of mechanical ventilation, haemodynamics, etc.^b^	×	×	×	×	×	×	×	×				
Additional clinical data collection, e.g., chest X-ray, CT, echocardiography^b^	×	×	×	×	×	×	×	×				
Lung function test, echocardiography									×	×	×	×
Record of any additional hospitalizations or ER visits									×^d^	×^d^	×^d^	×^d^
Clinical severity scores (GCS, SOFA, etc.)^b^	×	×	×	×	×	×	×	×				
WHO Clinical Ordinal Scale	×	×	×	×	×	×	×	×	×^d^	×^d^	×^d^	×^d^
Quality of life	×^d^							×^d^	×^d^	×^d^	×^d^	×^d^

^a^Visits may be conducted by phone

^b^These assessments are optional, only to be obtained if performed as part of standard of care

^c^Only performed if routine blood sampling is indicated

^d^Patient reported data that can be collected by phone due to isolation restrictions and follow-up visits conducted by phone

^e^Patients that remain in hospital beyond visit 7 will be assessed clinically. If no recovery is seen, study visits will continue until recovery or discharge. Else, in hospital, visits will end with V7

We will also recruit a representative cohort of outpatients with mild symptoms of COVID-19, in whom study visits and biosamplings are only performed at enrolment (V1) and at day 15 (V7) plus follow-up, provided that no hospitalization becomes necessary during the course of disease. Telephone interviews will be performed with outpatients to assess patient-reported health status between V1 and V7.

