### Quality assurance and control measures

A detailed data dictionary will define data to be collected on eCRF. Quality checks will be built into the data management system, including the possibility to generate queries, to ensure standardization and validity of the data collected. Any information that is not available to the investigators will be considered as missing. No assumptions will be made for missing data. Data monitoring of a randomly selected subset of collected data will be performed in the course of the study. Discussion of data collection techniques throughout the course of the study with investigators will ensure data quality and allow for adjustments.

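### No day-15 WHO ordinal scale score is scheduled for inpatients discharged before day 15, although the abstract names day 15 as an outcome time

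*Protocol article*

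**What the plan says.** - **Outcome time.** Abstract, Results: "Outcome measures include the WHO clinical ordinal scale on day 15". Clinical, functional and quality-of-life assessments at discharge and follow-up are listed beside it. No outcome is called primary.
- **When the scale is scored.** Methods, Data collection: "including the WHO 7 category ordinal scale [23] at study visits until day 15 and at discharge from hospital".
- **Inpatient schedule.** Table 1: "Visits will be conducted three times a week until discharge from hospital", on a grid described as "Monday/Wednesday/Friday starting day of enrolment". The first contact after discharge is V8, "6 weeks after enrolment", with a window of ± 1 week.
- **Scale row.** The Table 1 row "WHO Clinical Ordinal Scale" is marked at V1 to V7, at the discharge visit and at V8 to V11. Footnote d (patient-reported, may be taken by phone) is attached in this row only at V8 to V11. Footnote a (visit may be held by phone) is likewise attached only to V8 to V11.
- **Outpatients.** The paragraph below Table 1 describes mild outpatients, "in whom study visits and biosamplings are only performed at enrolment (V1) and at day 15 (V7) plus follow-up", as long as they are not admitted.
- **Missing data.** Quality assurance and control measures: information not available to the investigators counts as missing, and "No assumptions will be made for missing data".

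**The concern.** The outcome is tied to a fixed day, but for inpatients its collection is tied to location. A patient well enough to go home in the first two weeks leaves the visit schedule before the day on which the outcome is defined. Whether an inpatient has an observed day-15 score then depends on recovery, which is what the scale measures.

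The study aims to find prognostic scores and biomarkers and to describe short-term outcome. For those purposes the early-discharged inpatients are an informative group: ill enough to be admitted, yet quick to recover. Mild outpatients are scored at day 15 and so are patients still in hospital, so the gap falls between them. A discharge-day score does not replace a day-15 score, because a patient may be readmitted or die in between. The article also offers itself as a blueprint for other German centres, which would inherit the gap.

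**Working it through.** **1. The plan's own figure: V7 as day 15.** Take V1 as day 1. With enrolment on a Monday, the Monday/Wednesday/Friday grid gives V1 to V7 on days 1, 3, 5, 8, 10, 12 and 15. Wednesday and Friday enrolment also put V7 on day 15. V7 is therefore the day-15 visit, as the article says.

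**2. One early-discharged inpatient.** Suppose enrolment on a Monday and discharge on day 6.
- Scores in hospital: days 1, 3 and 5, plus the discharge visit on day 6.
- V7 (day 15): not held, because visits run until discharge and V7 carries no phone mark.
- V8: 42 ± 7 days after enrolment, that is, days 36 to 50 when enrolment is day 1.
- Gap from day 15 to the next score: 36 − 15 = 21 days at the least, 50 − 15 = 35 days at the most.

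A never-admitted outpatient enrolled on the same day has a V7 on day 15.

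**3. Size.** The article gives no discharge rate and no outpatient share, so both are assumed here:
- q = share of inpatients discharged alive before day 15;
- o = outpatient share of the cohort.

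Share of inpatients without a day-15 score = q. Share of the whole cohort without one = (1 − o) × q.

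| o | q = 30% | q = 50% | q = 70% |
|---|---|---|---|
| 0% | 30% | 50% | 70% |
| 30% | 21% | 35% | 49% |
| 50% | 15% | 25% | 35% |

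For example, with o = 30% and q = 50%: 0.70 × 0.50 = 35%.

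**4. Who supplies the day-15 values that do exist?** Count deaths as known. The share from inpatients still in hospital or dead is (1 − o)(1 − q) / [(1 − o)(1 − q) + o].
- o = 0%: 100%, whatever q.
- o = 30%: from 0.21/0.51 = 41% (q = 70%) to 0.49/0.79 = 62% (q = 30%).
- o = 50%: from 0.15/0.65 = 23% (q = 70%) to 0.35/0.85 = 41% (q = 30%).

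Dependence on still being in hospital is thus a statement about inpatients. Over the whole study it varies with the outpatient share.

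**The case against.** The strongest reply is that much of the day-15 status can be recovered. Discharged inpatients have a score at discharge and again from V8. Table 1 records further hospital stays and emergency visits at V8 to V11. Under Data management and storage, the enrolment log may be used to record outcomes and fill in missing data points. A full protocol or analysis plan, not shown, may define how the day-15 category is derived. This stands in part: whether a patient was back in hospital on day 15 can probably be established afterwards. Finer distinctions among patients at home may be lost, and no later rule can supply a contemporaneous score that was never taken.

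A reader might also infer more than the documents support:
- **That day-15 scores across the study come mainly from patients still in hospital.** Outpatients have a V7, and with enough of them this is not so (step 4 of the working).
- **That this is the main outcome.** The article ranks none, sets no sample size and describes a phenotyping cohort.
- **That early deaths and discharges are coded as missing.** The missing-data sentence concerns information unavailable to the investigators. In-hospital death and discharge are available to them, and the sections on post-mortem analysis and ethics show that deaths are expected to be known. The sentence does leave it unclear whether a discharge score may stand in for day 15.
- **That in-hospital categories would be inflated by a calculable factor.** That requires an analysis that drops every discharged and dead inpatient, and no such analysis is stated.
- **That V7 misses day 15.** Enrolment off the grid would move V7 by one or two days, which is ordinary visit tolerance.

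**Conclusion.** The point holds for inpatients discharged alive before day 15. The article names a day-15 outcome and schedules no day-15 score for them, while it does schedule one for mild outpatients. Among inpatients, direct observation therefore depends on not yet having gone home, and the recorded discharge and readmission data repair this only partly.

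The affected share of inpatients equals the share discharged alive before day 15: 30% to 70% over the assumed range. For the whole cohort this becomes 21% to 49% with 30% outpatients and 15% to 35% with 50% outpatients. All these shares are assumptions, as the article gives none. The existence of the gap rests on the visit schedule alone. The bias in any particular analysis cannot be stated from the document.

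**What to change.** 1. In Table 1 and the Data collection text, make the WHO scale a day-15 item for every participant: from the chart if in hospital, by a short phone call if discharged.
2. In the scale's row of Table 1, extend footnote d to V7. As printed, it covers only V8 to V11. The phone interviews with outpatients between V1 and V7 concern patient-reported health status, so they do not already provide this.
3. State that a death on or before day 15 is scored in the scale's death category. The article does not print the seven categories, so take the wording from the scale itself.
4. In Quality assurance and control measures, state that discharge and death are known states and not missing data.

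The cost is one short call per early-discharged inpatient and the changes of wording; no extra patients or blood samples are needed. The article says that recruitment has only recently begun. The change is worth making soon, because a score not taken on day 15 cannot be taken later.

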#### Serial bio-sampling, molecular and immunological phenotyping, and systematic biobanking

The molecular basis of the widely variable clinical course of COVID-19 is unknown. Many risk factors for severe disease, prognostic biomarkers, or correlates of protective immunity remain unclear. Several reports have indicated a central role for improper immune responses in COVID-19-associated lung damage and severe disease [25]. To elucidate the immunological basis for different courses of COVID-19 and the development of natural immunity, we have devised a detailed sequential deep phenotyping strategy, to decipher the composition and activation state of cellular and humoral components of the host immune response to SARS-CoV-2, employing high-resolution technologies including single-cell RNA-Sequencing and Cellular Indexing of Transcriptomes and Epitopes by Sequencing (CITE-Seq), T-cell receptor and B-cell receptor sequencing, Cytometry by Time-of-Flight (CyTOF), quantitative plasma proteomics, epigenetic profiling, as well as hypothesis-driven investigation and validation of individual biomarkers by conventional immunoassays.

As scientific data on clinical, cellular, and molecular aspects of COVID-19 are rapidly evolving, we will preserve high-quality biosamples, including cryopreserved immune cells, through a large-scale biobanking effort. An overview of the sample flow is shown in Fig. 1. Blood samples are collected three times per week in hospitalized patients, alongside blood drawing for routine laboratory analysis. Biobanking is organized in close cooperation with central biobank of Charité/BIH (ZeBanC) according to standard operational procedures (SOPs) and under certified conditions.

